## Abstract

**Background**: Photobiomodulation (PBM) therapy has shown potential in managing oral mucositis (OM), a frequent and painful side effect of radiotherapy or chemoradiotherapy in head and neck cancer patients. Although PBM is increasingly used in clinical settings, the optimal delivery method—transcutaneous or intraoral—remains undetermined. **Methods**: This prospective, single-center, randomized pilot study (clinicaltrials.gov NCT06458517) aims to compare the efficacy of transcutaneous versus intraoral PBM in preventing and managing OM in patients undergoing radiotherapy or chemoradiotherapy for cancers of the oral cavity or oropharynx. Participants will be randomized into two groups: one receiving intraoral PBM with the CareMin650™ device, and the other receiving transcutaneous PBM with the ATP38^®^ device. **Results**: Primary and secondary outcomes will include the incidence and severity of OM, treatment interruptions, patient-reported pain levels, and quality of life, assessed using validated tools. **Conclusions**: This study will provide comparative data on two PBM modalities, contributing to the development of standardized PBM protocols in supportive oncology care and informing future multicenter trials aimed at improving patient outcomes during radiotherapy for head and neck cancer.

## 1. Introduction

Head and neck cancers account for approximately 4–5% of all malignancies worldwide, with over 900,000 new cases annually. These cancers comprise a heterogeneous group of tumors arising in the upper aerodigestive tract, including the oral cavity, oropharynx, hypopharynx, nasopharynx, and larynx. The predominant histological type is squamous cell carcinoma, representing more than 90% of head and neck cancers [1]. Additional subtypes include salivary gland tumors, which are histologically diverse and relatively rare, and non-melanoma skin cancers of the head and neck region, which are common but often underreported.

In 2020, lip and oral cavity cancers accounted for approximately 389,846 new cases and 186,427 deaths globally, with particularly high incidence rates in South and Southeast Asia [2]. Oropharyngeal cancers represented over 106,000 cases and 52,000 deaths, with tobacco, alcohol, and HPV infection being key risk factors [3]. Nasopharyngeal cancers, although geographically concentrated in East and Southeast Asia, contributed to more than 120,000 new cases and 73,000 deaths worldwide [4]. Hypopharyngeal cancers, though less common, remain among the most lethal, with over 86,000 new cases and a high mortality-to-incidence ratio [2]. Salivary gland cancers accounted for approximately 55,000 new cases globally, with variable histology and outcomes depending on subtype and stage at diagnosis [4].

These cancers are frequently diagnosed at advanced stages, often due to late-onset symptoms and limited accessibility of certain anatomical sites. Consequently, patients commonly require multimodal treatment strategies, including surgery combined with radiotherapy and/or chemotherapy, either as neoadjuvant, adjuvant, or concomitant therapy. However, these therapies are often associated with debilitating side effects, among which oral mucositis (OM) is one of the most frequent and severe complications [5,6].

### 1.1. Oral Mucositis: A Major Clinical Challenge

OM is an acute inflammatory condition that affects 59–100% of patients receiving radiotherapy for oral cavity and oropharyngeal cancers, leading to painful ulcerative lesions that impair swallowing, nutrition, and overall quality of life [7,8]. Severe cases can result in treatment delays or dose reductions, which may compromise oncological outcomes [9,10,11,12]. Current treatment options, such as topical agents (e.g., medicated mouthwashes) and systemic analgesics, provide suboptimal relief, highlighting the urgent need for more effective strategies [13,14].

Several alternative or adjunctive strategies have been investigated for the management of OM in cancer patients. Histatin-5 mucoadhesive gel, a salivary antimicrobial peptide formulation, has shown promising results in preclinical and in vivo studies for promoting mucosal healing [15]. Bioadhesive agents, which form protective films over ulcerated mucosa, have also demonstrated efficacy in reducing mucositis severity and improving patient comfort, as confirmed by a recent systematic review and meta-analysis [16]. Furthermore, herbal medicine is being explored as a supportive care option to alleviate radiation-induced mucosal toxicity, particularly in traditional Asian medicine contexts [17]. At the molecular level, the keratinocyte growth factor (KGF)/KGF receptor (KGFR) pathway has been identified as a dual therapeutic target for both epithelial repair and cancer regulation, offering potential in mucosal protection strategies during cancer treatment [18].

These approaches complement light-based therapies, which remain among the most extensively studied interventions for mucositis prevention and treatment in oncology [10].

Radiation-induced OM is a multi-phase pathological process triggered by direct cytotoxic damage to epithelial cells, leading to inflammatory cascades, reactive oxygen species generation, and further tissue breakdown. Predictive modeling has identified key risk factors for severe OM, including treatment acceleration, mean radiation dose to the oral cavity, smoking status, and patient gender [19,20].

Given the complexity of OM pathogenesis and its profound impact on patient outcomes, novel therapeutic approaches are warranted.

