## 2. Materials and Methods

### 2.1. Study Setting

This randomized pilot study will be conducted at the Institut de Cancérologie Strasbourg Europe (ICANS), France, in the University Department of Radiotherapy and the Department of Oncology Supportive Care. The study will aim to compare the efficacy of transcutaneous and intraoral PBM in preventing and managing OM in patients receiving radiotherapy for cancers of the oral cavity and oropharynx. The study will follow a randomized 1:1 allocation of patients to either the transcutaneous PBM or intraoral PBM group, with stratification based on tumor location, prior surgery, and chemotherapy regimen.

This study was registered on clinicaltrials.gov in November 2024 (NCT06458517).

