### 2.5. Data Collection

Data will be collected from electronic medical records and will include demographics, clinical history, treatment details, and outcomes. Weekly evaluations of OM will be performed by clinicians independent from PBM administration and unaware of group allocation using National Cancer Institute Common Terminology Criteria for Adverse Events (NCI-CTCAE) v5.0 criteria. Additional data will include visual analog scale pain scores, the quality of life questionnaires European Organisation for Research and Treatment of Cancer Quality of Life Questionnaire–Core 30 (EORTC QLQ-C30) and European Organisation for Research and Treatment of Cancer Quality of Life Questionnaire–Head and Neck Module (EORTC QLQ-HN35) [37,38], and nutritional intake using the Simple Evaluation of Food Intake (SEFI) tool.

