### 2.6. Statistical Analysis

Descriptive statistics will summarize the patient demographics and clinical characteristics. Quantitative variables will be expressed as mean ± standard deviation, while categorical variables will be presented as frequencies and percentages. Between-group comparisons will be conducted using appropriate statistical tests, including t-tests for continuous data and chi-squared tests for categorical data. A significance level of *p* < 0.05 will be considered statistically significant.

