### 2.8. Objectives

#### 2.8.1. Primary Endpoint

The primary outcome measure of this study is the reduction in the incidence of OM (grade ≥ 2) in patients undergoing radiotherapy or chemoradiotherapy for cancers of the oral cavity or oropharynx. The comparison will be based on the method of PBM delivery: transcutaneous versus intraoral.

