## Figures and Tables

**Figure 1 jcm-14-02430-f001:**
[figure not shown]
RADIO-PBM trial schema. Abbreviations: PBM: photobiomodulation; EORTC QLQ-C30, European Organisation for Research and Treatment of Cancer Quality of Life Questionnaire–Core 30; QLQ-HN35, European Organisation for Research and Treatment of Cancer Quality of Life Questionnaire–Head and Neck Module.

**Table 1 jcm-14-02430-t001:** Inclusion and exclusion criteria.

Inclusion Criteria	Exclusion Criteria
Adult patients diagnosed with cancer of the oral cavity or oropharynx. Scheduled to receive radiotherapy or chemoradiotherapy. Karnofsky Performance Status (KPS) > 60%. Fluent in French and able to provide informed consent. Enrolled in the French national healthcare system.	Allergy to polyurethane or contraindications to PBM. Prior irradiation to the head and neck region. Pregnant or lactating women. Presence of medical devices such as pacemakers or epilepsy.

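### None of the four mucositis risk factors the article names is stratified on, and the stated tests adjust for none: pre-specify adjustment for planned oral-cavity dose

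*Protocol article*

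**What the plan says.** Section 1.1 reports earlier modelling work in these terms: "Predictive modeling has identified key risk factors for severe OM", "including treatment acceleration, mean radiation dose to the oral cavity, smoking status, and patient gender". The four factors are not ranked, and the outcome they predict is severe OM.

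Section 2.1 sets 1:1 randomisation "with stratification based on tumor location, prior surgery, and chemotherapy regimen". None of the four factors is among these three.

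Section 2.6 plans between-group comparisons by suitable tests, "including t-tests for continuous data and chi-squared tests for categorical data". It names no covariate model. Section 2.8.1 defines the primary endpoint as the incidence of OM of grade 2 or worse, which is broader than severe OM.

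On radiotherapy, Table 1 asks only for patients "Scheduled to receive radiotherapy or chemoradiotherapy", so eligibility does not narrow the range of dose or fractionation. Section 2.5 says the data collected "will include demographics, clinical history, treatment details, and outcomes". Section 2.4 mentions confounding, but only in connection with recording concomitant treatments. Sections 3 and 4 call the sample small without giving a number.

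**The concern.** The article identifies pre-treatment variables that predict mucositis and then makes no stated use of them. Oral-cavity dose stands out because the treatment plan fixes it before the first photobiomodulation (PBM) session, so it is a clean baseline covariate. The concomitant treatments in section 2.4 are not: they are mostly given after randomisation and can respond to OM itself, so adjusting for them is hazardous.

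At stake is how one small randomisation will be read. Section 2.10.2 expects the trial to identify the more effective delivery route. If one arm happens to receive more dose to the oral cavity, an unadjusted comparison of grade 2 or worse OM cannot separate that from the effect of the route.

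**Working it through.** The article states no sample size, event rate, effect size or power, so there is no figure of its own to reproduce. Every n, rate and odds ratio below is an assumption, shown as a range.

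**1. Factors side by side.** Named risk factors: acceleration, mean oral-cavity dose, smoking, gender. Stratification factors: tumour location, prior surgery, chemotherapy regimen. The overlap is nil. Tests named: t-test and chi-squared, both unadjusted.

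**2. Chance imbalance in dose.** For a continuous covariate left unstratified, the standardised difference between arms has mean 0 and SE = √(2/n), with n per arm.

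- n = 20: SE = √(2/20) = 0.316; P(|d| > 0.3) = 2[1 − Φ(0.3/0.316)] = 0.34
- n = 30: SE = √(2/30) = 0.258; P(|d| > 0.3) = 2[1 − Φ(0.3/0.258)] = 0.25

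Other thresholds, at 20 / 30 / 50 per arm: P(|d| > 0.25) = 43% / 33% / 21%; P(|d| > 0.5) = 11% / 5% / 1%. For a binary factor with 50% prevalence (smoking or sex, say), the SE is √(0.5/n), and a difference of at least 20 percentage points has probability 21% / 12% / 5%.

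The figures for dose are upper limits. If the stratification factors explain a share R² of the variance in dose and are balanced, the SE falls to √(2(1 − R²)/n). The article gives nothing from which to set R².

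**3. What an imbalance does to the endpoint.** If the odds of OM double per SD of dose, a 0.3 SD imbalance alone gives an odds ratio of exp(0.3 × ln 2) = 1.23, a log-odds ratio of 0.21. With 60% of patients having the event, the SE of the log-odds ratio is √(2/(n × 0.6 × 0.4)) = 0.65 at n = 20 and 0.53 at n = 30. The shift is therefore about 0.3 to 0.4 of one SE.

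For a larger imbalance, with dose more than 0.5 SD higher in one arm and no treatment effect, the simulated mean risk difference at 20 and 30 per arm was about 6 percentage points (odds ratio 1.5 per SD) to 11 points (2.5 per SD). The SE of an unadjusted risk difference at 60% is √(2 × 0.6 × 0.4/n) = 15 points at n = 20 and 13 points at n = 30.

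**4. What adjustment gains.** A simulation (1,500 runs per setting, 60% control rate, treatment log-odds ratio 0 or −1.0) compared the chi-squared test with a likelihood-ratio test from a logistic model containing dose.

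| n per arm | OR per SD | Power, unadjusted | Power, adjusted |
|---|---|---|---|
| 20 | 1.5 | 30% | 34% |
| 20 | 2.5 | 26% | 34% |
| 30 | 1.5 | 46% | 47% |
| 30 | 2.5 | 41% | 47% |
| 50 | 1.5 | 67% | 68% |
| 50 | 2.5 | 61% | 65% |

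With no treatment effect, the unadjusted test rejected in 4.6% to 5.7% of runs. The adjusted test rejected in 6.1% to 7.2% at n = 20, so part of the apparent gain there is small-sample inflation of the likelihood-ratio test. A single power figure near 45% has a Monte Carlo SE of √(0.45 × 0.55/1500) = 1.3 points.

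**The case against.** The strongest reply is that this rests on absence. The test list in section 2.6 is introduced as non-exhaustive, the article condenses a fuller protocol, and an analysis plan that is not shown may contain a covariate model. That stands as far as it goes: a reader might infer that the trial as a whole adjusts for nothing, and the document does not support that. It supports only that the comparisons stated here are unadjusted.

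A reader might also infer that dose is the main driver of the primary endpoint. Section 1.1 does not rank its four factors, and it concerns severe OM, not grade 2 or worse. Nor does the document show that the four go wholly unbalanced: tumour location and prior surgery plausibly track oral-cavity dose, though that is a judgement the article does not make.

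Nor is chance imbalance bias. Randomisation already allows for it, and the simulated type I error confirms this. The shift from a 0.3 SD imbalance lies well within ordinary sampling error, as shown above. It would also be wrong to say that adjustment narrows the interval on the odds-ratio scale, because the SE of a log-odds ratio does not shrink when a covariate is added to a logistic model.

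Finally, the relevant data may already be collected: demographics, clinical history and treatment details could cover all four factors. That makes the change cheaper. It does not replace stating in advance how dose will be used.

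**Conclusion.** The point holds in a limited form. The article names four risk factors, stratifies on three others, and names only unadjusted comparisons. The consequence is some loss of precision and a harder reading of a single small result; the type I error is not affected.

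The size is modest. For an assumed 20 to 30 per arm, the chance of a dose imbalance above 0.3 SD is at most about 34% to 25%. At 30 per arm, adjustment raises simulated power by about 6 points if dose is a strong predictor (odds ratio 2.5 per SD) and by about 1 point if it is a weaker one (1.5 per SD). Where the trial falls in that range depends on the sample size and on how strongly dose predicts grade 2 or worse OM, and the article gives neither.

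**What to change.** In section 2.6, pre-specify for the primary endpoint a covariate-adjusted comparison that includes planned mean oral-cavity dose, with the stratification factors alongside it as far as the sample size allows. Take the dose from the approved treatment plan before the first PBM session. Do not use delivered dose: section 1.1 says severe OM can lead to delays or dose reductions, and section 2.8.2 counts treatment interruptions as an outcome, so delivered dose can itself be altered by OM.

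Report the result as a standardised risk difference with its confidence interval. Tabulate fractionation, smoking and sex by arm, and use them only in a supporting analysis. Leave the randomisation as it is, since four more stratification factors would give sparse strata. Fix the model before any outcome data are seen, because a covariate chosen later would look data-driven.

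The cost is a few baseline fields, possibly already collected, and one extra model parameter in a small trial. Eligibility, visits and care do not change.

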### 1.2. Photobiomodulation Therapy: A Promising Approach

Photobiomodulation (PBM), the application of low-level light therapy, has emerged as an innovative and promising approach for OM prevention and management. Recent evidence supports its ability to reduce inflammation, accelerate tissue healing, and alleviate pain without significant adverse effects [10,21,22,23].

However, clinical implementation remains inconsistent, primarily due to a lack of standardized protocols. PBM can be delivered using two main approaches:Intraoral PBM, where light is applied directly to the affected mucosa, ensuring targeted irradiation.Transcutaneous PBM, a non-invasive method where light is applied externally through the skin, though tissue penetration may be a limiting factor [24].

Several clinical trials have demonstrated the efficacy of PBM in reducing OM severity and improving patient outcomes. A phase II trial reported that prophylactic PBM significantly lowered the incidence of severe OM in patients undergoing concurrent chemoradiation, with a severe OM rate of only 23%, markedly lower than historical controls [25]. Additionally, preconditioning with PBM before chemotherapy has been shown to prevent mucositis onset in up to 86.7% of patients, further highlighting its role in improving quality of life and treatment adherence [26].

Moreover, emerging evidence suggests that PBM may not only alleviate OM symptoms but also contribute to improved survival rates. Some studies indicate a significant correlation between the number of PBM sessions and increased overall survival in patients undergoing chemoradiation [27].

Despite these promising findings, concerns regarding PBM’s potential effects on tumor progression persist. However, recent research has suggested that PBM does not compromise oncological outcomes and may even enhance the immune response during cancer treatment [23]. This has led the World Association for Photobiomodulation Therapy (WALT) to establish evidence-based recommendations supporting PBM for OM management and emphasizing the need for standardized treatment protocols [28].

While systematic reviews and meta-analyses generally support the efficacy of PBM, a recent umbrella review found that the overall quality of evidence remained low, underscoring the necessity for high-quality randomized controlled trials to refine PBM protocols and confirm its benefits [13]. Despite these promising findings, PBM implementation in clinical practice remains inconsistent, with no consensus on the optimal treatment parameters, including the choice between transcutaneous and intraoral delivery methods [29].

### 1.3. Justification for the Comparison Between Intraoral and Transcutaneous PBM

PBM relies on the application of low-intensity light to stimulate biological processes, particularly the reduction in inflammation and the acceleration of tissue repair. The effectiveness of this approach is influenced by several parameters, including wavelength, applied dose, and the depth of light penetration in biological tissues. Studies on light penetration in both intraoral and extraoral tissues have demonstrated that wavelengths in the red spectrum (600–700 nm) and near-infrared spectrum (700–1000 nm) exhibit different penetration capacities depending on the medium they traverse. Intraoral PBM, applied directly to the oral mucosa, allows for the efficient transmission of photon energy to the epithelial and subepithelial layers, thereby maximizing local bio-stimulation [21]. Additionally, studies have shown that the extraoral application of near-infrared phototherapy can significantly reduce mucositis-related pain in patients undergoing hematopoietic stem cell transplantation, suggesting that transcutaneous PBM may be effective despite potential energy loss due to tissue absorption [30].

A study by Jagdeo et al. evaluated light diffusion through various thicknesses of human tissues and demonstrated that photon intensity decreased exponentially with depth, particularly in highly vascularized and dense tissues [31]. This suggests that intraoral PBM may have a significant advantage in directly targeting mucosal lesions, whereas transcutaneous PBM may be more suitable for deeper or less accessible areas (Huang et al., 2009) [32]. Bensadoun et al. highlighted that while both intraoral and extraoral PBM approaches were effective for managing OM, intraoral PBM ensured the direct irradiation of mucosal tissues, optimizing energy absorption and therapeutic efficacy [22]. In contrast, extraoral PBM, particularly with near-infrared wavelengths, may reach intraoral structures indirectly but is subject to potential energy loss due to absorption and scattering by intermediate tissues.

Recent clinical and preclinical studies have further explored the efficacy of both approaches, highlighting the need for a direct comparative analysis. Ramos-Pinto et al. conducted a randomized clinical trial in hematopoietic stem cell transplant patients and found that intraoral and extraoral PBM were both effective in reducing mucositis severity, with intraoral PBM providing a more targeted effect [33]. Similarly, Thieme et al. demonstrated in a chemotherapy-induced mucositis animal model that intraoral PBM promoted faster healing, whereas extraoral PBM, despite being less direct, still contributed to mucosal recovery [34]. Adnan et al. emphasized the need for optimized dosimetric parameters in extraoral PBM to ensure sufficient photon penetration and therapeutic effectiveness [35]. These findings suggest that while intraoral PBM may offer superior localized effects, extraoral PBM remains a promising alternative, particularly when intraoral application is not feasible.

This randomized pilot study aims to compare the efficacy of transcutaneous and intraoral PBM in preventing and managing OM in patients undergoing radiotherapy for oral cavity and oropharyngeal cancers. By addressing gaps in clinical practice, this study seeks to provide evidence that can contribute to the standardization of PBM protocols and ultimately enhance patient care outcomes

## 2. Materials and Methods

### 2.1. Study Setting

This randomized pilot study will be conducted at the Institut de Cancérologie Strasbourg Europe (ICANS), France, in the University Department of Radiotherapy and the Department of Oncology Supportive Care. The study will aim to compare the efficacy of transcutaneous and intraoral PBM in preventing and managing OM in patients receiving radiotherapy for cancers of the oral cavity and oropharynx. The study will follow a randomized 1:1 allocation of patients to either the transcutaneous PBM or intraoral PBM group, with stratification based on tumor location, prior surgery, and chemotherapy regimen.

This study was registered on clinicaltrials.gov in November 2024 (NCT06458517).

